#### Birth-related data collection

After the expected date of delivery, research nurses at each site will collect and input into the trial database data regarding parity, baby’s birth date and weight.

### Data management

The data management process will be run by York Trials Unit. The protocol was built on the platform from the phase II trial [34]. This has been improved and updated by York Trials Unit in conjunction with the central trial team ([name]) and has been used for submissions for regulatory approval.

The database is a modified version of that used in CPIT II. York Trials Unit, central trial management in Glasgow and research staff at one of the recruiting sites have contributed to the design of the modified version.

Data entry will be completed by trained research staff at local sites.

### Statistical methods

Statistical analysis will be conducted by York Trials Unit ([name]). All analyses will be carried out using the intention-to-treat principle unless stated otherwise. Treatment effect estimates will be presented along with the corresponding 95% confidence interval, and statistical tests will be two-sided at the 5% level, unless otherwise stated.

#### Primary outcome analysis

Primary outcome analysis will be by intention to treat as the intervention is the offer of a financial incentive to engage with SSS and quit smoking. Logistic regression will adjust for maternal age, years of smoking, deprivation score, level of smoking and site.

#### Secondary outcome analysis

Engagement with SSS and self-reported smoking status at 4 weeks will both be analysed using a logistic regression model adjusting for the same covariates as the primary analysis. Continuous and point abstinence (i.e. regardless of whether participants were abstinent in late pregnancy) outcomes obtained at 6 months post-partum [28] will be calculated using logistic regression also adjusting for the same covariates as the primary outcome analysis. For each of the following covariates, tests for interaction with the treatment group will be performed: age of mother, years of smoking, deprivation score and level of smoking. Effects on the length of neonatal unit stays will be examined.

Birth weight will be analysed using a linear regression model adjusting for key prognostic variables including age, site, height and weight of mother at early pregnancy. The intention-to-treat estimate will be severely diluted due to low smoking cessation rates and the ‘per protocol’ analysis will be biased by confounding. Consequently, we will also utilise an instrumental variable approach—complier average causal effect analysis—which will estimate the true impact of incentive-induced smoking cessation on birth weight [35].

Differences by subgroup (e.g. site, deprivation, age group) will be explored and reported as per the CHAMP guidelines [36].

A meta-analysis including data collected in the feasibility study in Glasgow on 612 participants [24] will be undertaken.

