### Sample size and recruitment

The sample size for this phase III trial is 940 pregnant smokers. This was calculated on the basis of the primary outcome. A total of 940 participants (470 in each group) will detect a clinically significant doubling of the cotinine-validated quit rate from 7% with usual care alone to at least 14% with usual care plus the offer of financial voucher incentives, with 90% power at the 5% significance level allowing 15% loss to follow-up.

Eligible pregnant smokers will be enrolled over a 26-month period from February 2018 to March 2020. Recruiting for 18 months would have allowed all participants to be followed up to the secondary outcome point 6 months after birth. Recruiting for 26 months (including a 3-month funded extension from CRUK—see Funding for confirmation) has allowed an additional 8 months with recruitment slower than expected whilst allowing the first 75% of participants recruited to be followed up to the secondary outcome point 6 months after birth. This compromised 6-month post-partum follow-up was agreed with the funders, the ethics committee and the sponsor prior to the study start in September 2017.

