#### Follow-up 3: 12 weeks post quit date

For those women in the intervention group who were confirmed quit at 4 weeks, trial research staff will contact their local SSS 8 weeks later to obtain their smoking status and CO breath test result as recorded by the SSS. Where this is not available from the SSS trial, research nurses will collect this directly from the woman. This information will be entered into the trial database. If the CO result is at or below the accepted level for a non-smoker at the site, a £100 voucher will automatically be dispatched

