#### Missing data

Where there are missing data for the primary outcome (i.e. smoking status) it will be assumed that women are continuing to smoke. This assumption will be examined by testing residual blood samples (taken for other reasons in late pregnancy) for cotinine, as in the feasibility trial [24]. This assumption will also apply to the 6-month post-partum secondary outcome of smoking status. Other secondary outcomes (e.g. birth weight) are collected routinely and will have few missing data. Long-term outcome data collection will be planned from participants and offspring to inform additional follow-up studies.

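### The birth-weight CACE is said without condition to give the true effect of quitting, but no abstinence measure the trial collects can support that, and the bias could run either way

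*Protocol article*

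**What the plan says.** Birth weight is a secondary outcome. Under Secondary outcome analysis it is analysed first by linear regression, "adjusting for key prognostic variables including age, site, height and weight of mother at early pregnancy". The same paragraph expects dilution of the ITT estimate and confounding of a per-protocol estimate. It therefore adds an instrumental variable analysis, the CACE, "which will estimate the true impact of incentive-induced smoking cessation on birth weight". The article attaches no condition to that statement and does not name the exposure used.

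The following sections bear on the claim:

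- **Primary outcome:** verified abstinence of at least 8 weeks, assessed at 34–38 weeks of gestation.
- **Follow-up 1 and 2:** £50 for engaging and setting a quit date, and £50 for a CO-validated quit 4 weeks after that date. Where the service has no CO reading at 4 weeks, research nurses obtain one for incentive-arm women. Control readings are used only if the service already holds them.
- **Follow-up 3** (incentive arm only): "If the CO result is at or below the accepted level for a non-smoker at the site, a £100 voucher will automatically be dispatched".
- **Missing data:** "Where there are missing data for the primary outcome (i.e. smoking status) it will be assumed that women are continuing to smoke". The rule is to be examined with residual blood cotinine. Birth weight is expected to have few missing values.
- **Birth-related data collection:** research nurses record "data regarding parity, baby’s birth date and weight".

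**The concern.** A CACE with randomisation as the instrument recovers the effect of an exposure only if allocation acts on the outcome solely through that exposure (the exclusion restriction). Here the vouchers reward several steps before late pregnancy. Suppose a woman stops for some weeks because of the vouchers and relapses before 34–38 weeks. She has had incentive-induced cessation but would count as unexposed under a late-pregnancy definition. Any gain in her baby's weight then enters the numerator of the CACE ratio and not the denominator.

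The denominator also depends on how missing smoking status is handled, whereas the numerator rests on nearly complete birth records.

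At stake is what the birth-weight analysis can conclude. Because the text describes the ITT estimate as diluted and the per-protocol estimate as biased, it points readers to the CACE as the answer. The Discussion says the trial is meant to inform an update of national guidance.

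**Working it through.** **The plan's own figure.** Sample size and recruitment assumes a "doubling of the cotinine-validated quit rate from 7% with usual care alone to at least 14% with usual care plus the offer", "with 90% power at the 5% significance level allowing 15% loss to follow-up"; Statistical methods adds that "statistical tests will be two-sided at the 5% level". The pooled two-proportion formula gives 401 per arm. Then 401/0.85 = 472 per arm, or 944 in total. With unpooled variance it is 398 per arm, or 938 in total. The stated 940 is reproduced, so 14% − 7% = 7 percentage points is used below as the true difference in late-pregnancy cessation. The article gives no figure for birth weight or the CACE.

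**The ratio.** Unadjusted, CACE = (ITT effect on birth weight) / (between-arm difference in recorded exposure). Let B be the birth-weight effect of sustained cessation. All factors below are estimate divided by B, with late-pregnancy abstinence taken as the exposure.

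**Step 1: temporary quits.** Let d be the extra share of incentive-arm women who quit and relapse, and r the fraction of B that they gain. Then ITT = 0.07B + d·r·B, and the factor is 1 + d·r/0.07. Both d and r are assumptions.

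| d | r | Factor |
|---|---|---|
| 2 points | 0.25 | 1 + 0.005/0.07 = 1.07 |
| 4 points | 0.5 | 1 + 0.02/0.07 = 1.29 |
| 7 points | 0.5 | 1 + 0.035/0.07 = 1.50 |
| zero, or r = 0 | – | 1.00 |

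**Step 2: missing coded as smoking, equal loss m in both arms.** If lost women quit at q times the observed rate, the factor is 1 + m·q/(1 − m).

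| Loss m | Source | q = 0 | q = 0.5 | q = 1 |
|---|---|---|---|---|
| 10% | follow-up target of about 90% | 1.00 | 1.06 | 1.11 |
| 15% | sample-size allowance | 1.00 | 1.09 | 1.18 |

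**Step 3: unequal loss.** At q = 1 the recorded difference is 0.14(1 − m1) − 0.07(1 − m0), where m1 is incentive-arm loss and m0 control loss. It exceeds 0.07 once m0 > 2·m1. With control loss of 20% and incentive loss of 5% (assumed), the difference is 0.133 − 0.056 = 0.077 and the factor is 0.07/0.077 = 0.91. At q = 0.5 it is 0.94.

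**Step 4: false quits.** Follow-up 4 recognises that the primary outcome might be gamed. If g points of incentive-arm women are falsely recorded as quit (assumed), the factor is 0.07/(0.07 + g): 0.88 for 1 point and 0.70 for 3 points.

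**Step 5: combination.** Because each step changes either the numerator or the denominator, they can be put together.

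- Small temporary-quit effect with 3 points of false quits: (0.07 + 0.005)/(0.07 + 0.03) = 0.75.
- Large temporary-quit effect with 15% equal loss and q = 1: (0.07 + 0.035)/(0.07 × 0.85) = 1.76.

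The assumed inputs therefore span both understatement and overstatement.

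**Precision, for context.** With an assumed SD of 500–600 g, the ITT standard error is SD × √(2/470) = 32.6–39.1 g. Divided by 0.07, this gives a CACE standard error of 466–559 g, a 95% interval of about ±0.9 to ±1.1 kg. The first-stage F is 0.07² / ((0.0651 + 0.1204)/470) = 12.4.

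**The case against.** The strongest reply is that the article names neither the CACE exposure nor its missing-data rule. The Missing data section applies the smoking assumption to the primary outcome and to status at 6 months, and does not mention the CACE. A condensed article may leave both to the full protocol or analysis plan. This stands: a reader might infer that the exposure is defined so as to ignore earlier quits and to code missing as smoking, but the document does not say so, and the absence of the definition is not a fault. It does not rescue the claim, however. An exposure based on 4-week status would be measured less completely in controls, and 12-week status is sought only in the incentive arm. None of the collected measures makes the unconditional statement correct.

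A reader might also infer that the CACE is inflated by construction. Steps 2 to 4 show otherwise. Missing coded as smoking does nothing if lost women do smoke, and the article itself is concerned about loss among controls and about gaming, both of which can push the estimate down.

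Other parts of the reply also stand:

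- ITT is already the first analysis of birth weight, and residual blood testing is already planned.
- The covariate list is introduced by a word that leaves it open, so parity and smoking level are not excluded. Omitting them would cost precision and would not bias a randomised comparison.
- A wide interval does not make a supplementary analysis wrong, because 95% intervals are promised and would show it.
- A reader might suppose that this estimate feeds the lifetime cost-effectiveness model. The article does not say so and leaves the economic methods to a separate paper.

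**Conclusion.** The point holds as a misstatement of what the analysis can deliver. The CACE estimates the effect of cessation only under an exclusion restriction that the staged vouchers put in doubt, and only for an exposure that is recorded correctly. If late-pregnancy abstinence is the exposure, temporary quits may inflate the estimate by a factor of about 1.07 to 1.50, given d of 2–7 points and r of 0.25–0.5, and by nothing if either is zero. Coding missing as smoking may add 0–11% at 10% equal loss or 0–18% at 15%. Control loss above about twice incentive-arm loss, or false quits in the incentive arm, would reduce it. The net direction cannot be stated in advance. The values of d, r, q, the unequal-loss split, the false-quit rate and the SD are assumptions and do not come from the article. The primary analysis and the ITT birth-weight result are unaffected.

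**What to change.** 1. Replace the claim of true impact with an exploratory CACE estimate, conditional on the exclusion restriction and secondary to the ITT result already planned.
2. Report the CACE twice: with missing status coded as smoking, and with multiple imputation informed by residual-blood cotinine. Residual blood will cover only some women, since it is used where available and its consent item is optional.
3. Add a sensitivity analysis with exposure defined as a 4-week quit recorded by the stop smoking service or a verified late-pregnancy quit. Use service records only in both arms, so that nurse-collected readings in the incentive arm do not enter. Read the result as a bracket: short quits made outside the service are unrecorded, which may enlarge the between-arm difference and push the estimate down.
4. Name parity and baseline smoking level among the birth-weight covariates, for precision. Both are already collected.

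The cost is a wording change, a few extra model runs on data already planned, and a weaker headline claim for this analysis.

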#### Missing data

Where there are missing data for the primary outcome (i.e. smoking status) it will be assumed that women are continuing to smoke. This assumption will be examined by testing residual blood samples (taken for other reasons in late pregnancy) for cotinine, as in the feasibility trial [24]. This assumption will also apply to the 6-month post-partum secondary outcome of smoking status. Other secondary outcomes (e.g. birth weight) are collected routinely and will have few missing data. Long-term outcome data collection will be planned from participants and offspring to inform additional follow-up studies.

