### Need for a further trial

The context within which incentives are offered is important. Socio-demographic, geographic and organisation differences may affect future transferability of the intervention and the potential to implement a sustainable intervention in the long term [25, 26]. Adding incentives to a range of SSS models in different areas of the UK serving varied population groups needs to be tested before clear recommendations can be made.

In addition, further evidence is required to inform the cost-effectiveness debate of incentive-based schemes. The economic analysis from our feasibility trial [23] indicated relapse post-partum was the biggest area of uncertainty. Six months is the recommended period to measure long-term abstinence [27], as those abstinent at this time point tend to remain smoke-free in the long term [28].

A pivotal phase III multi-centre UK trial that includes cessation outcomes to 6 months after birth is therefore required to be able to recommend changes in policy and practice [15], and thus for SSS funders (such as the NHS or local government in the UK) to consider this approach to smoking cessation as part of mainstream services.

The proposed study will assess whether promising feasibility trial findings [24] can be transferred to other UK sites with different SSS configurations and population groups. If found to be effective and cost-effective in this multi-site trial, the simple novel ‘bolt-on’ nature of the intervention will make the trial results generalisable to a wide range of SSS and population groups, and will allow easier transfer of the intervention to other SSS within the UK and other parts of the world.

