#### Follow-up 5: 6 months post-partum

Similar to the late pregnancy follow-up, all women will be contacted at 6 months after their expected delivery date to ascertain their smoking status and collect a saliva/urine sample for those women who self-report as quit. Quit status 6 months after birth will be ascertained by two sets of questions:
‘Have you smoked in the last 8 weeks?’ If yes, ‘Have you smoked more than 5 cigarettes in that time?’‘Have you smoked since your baby was born?’ If yes, ‘Have you smoked more than 5 cigarettes in total since your baby was born?’

Follow-up procedures (i.e. number of contact attempts, data collection and saliva/urine sample collection and assay) will be the same as those described for the late pregnancy follow-up. Biological samples of saliva and urine will not be available for use by other researchers.

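### The 6-month missing-equals-smoking rule does not exempt the roughly 25% of women whom the plan does not expect to follow that far, so absolute 6-month quit rates could be understated by a quarter

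*Protocol article*

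**What the plan says.** All references are to the Protocol article.

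- **Sample size and recruitment** explains that recruitment was lengthened to 26 months, "whilst allowing the first 75% of participants recruited to be followed up to the secondary outcome point 6 months after birth". The shortfall was planned: "This compromised 6-month post-partum follow-up was agreed with the funders, the ethics committee and the sponsor prior to the study start in September 2017".
- **Follow-up 5: 6 months post-partum** states that "all women will be contacted at 6 months after their expected delivery date to ascertain their smoking status". **Participant timeline and data collection** likewise gives one range for total study time, 42–62 weeks, for every participant, with follow-up running to 6 months after birth.
- **Missing data** sets the primary rule: "Where there are missing data for the primary outcome (i.e. smoking status) it will be assumed that women are continuing to smoke". It then extends it: "This assumption will also apply to the 6-month post-partum secondary outcome of smoking status". The only check offered is at the earlier time point: "This assumption will be examined by testing residual blood samples (taken for other reasons in late pregnancy) for cotinine".
- **Statistical methods** makes intention to treat the default for all analyses, allowing stated exceptions. None is stated for the 6-month outcomes under Secondary outcome analysis or Missing data.
- **Secondary outcomes** lists two 6-month abstinence endpoints, point and continuous, both as proportions of women.

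**The concern.** Counting missing as smoking is a convention for women who were due an assessment and could not be reached. It rests on the idea that silence is informative about smoking. A woman whose 6-month date falls after the study has closed is not silent: nobody was due to ask her. Her missing status reflects the calendar and says nothing about whether she smokes.

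The document states the rule for the 6-month outcome, states that about a quarter of women will not reach that point, and does not separate the two kinds of missing value. The sections also disagree on whether everyone is followed to 6 months.

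At stake are the absolute 6-month quit rates, the risk difference, and anything computed from them. This matters here because the background says the feasibility trial's economic analysis "indicated relapse post-partum was the biggest area of uncertainty", and gives that as a reason for extending outcomes to 6 months. A late-recruited woman who had quit by late pregnancy would, under the literal rule, be recorded as not continuously abstinent without ever being asked. The residual-blood check uses late-pregnancy samples and cannot test the assumption at 6 months.

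**Working it through.** **Inputs from the document:** 940 women, 470 per arm, 1:1; 7% v 14% late-pregnancy quit rates; 90% power; two-sided 5%; 15% loss; 75% of recruits followed to 6 months.

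**Step 1. Reproduce the plan's own figure.** Two proportions, pooled variance under the null, no continuity correction:

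n per arm = [1.96·√(2 × 0.105 × 0.895) + 1.2816·√(0.07 × 0.93 + 0.14 × 0.86)]² / 0.07² = 401

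401 / 0.85 = 472 per arm, 944 in total. With unpooled variance: 398, then 398 / 0.85 = 469 per arm, 938 in total. The stated 940 is reproduced. It concerns the primary outcome, for which all women are to be followed up, so nothing below affects it.

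**Step 2. Women with no planned 6-month assessment.** 0.25 × 940 = 235, about 117–118 per arm. The remaining 0.75 × 940 = 705 is about 352 per arm.

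**Step 3. Effect of the literal rule on the rates.** If the 235 enter the denominator as smokers, then in each arm:

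recorded rate = 0.75 × (rate among women due) + 0.25 × 0

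This holds even with perfect follow-up of everyone who was due. The document gives no 6-month quit rates, so the rates below are assumptions.

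| Assumed rates among women due | Recorded | Risk difference (points) | Risk ratio | Odds ratio |
|---|---|---|---|---|
| 3% v 6% | 2.25% v 4.5% | 3.0 → 2.25 | 2.0 → 2.0 | 2.06 → 2.05 |
| 4% v 8% | 3% v 6% | 4.0 → 3.0 | 2.0 → 2.0 | 2.09 → 2.06 |
| 5% v 10% | 3.75% v 7.5% | 5.0 → 3.75 | 2.0 → 2.0 | 2.11 → 2.08 |
| 7% v 14% | 5.25% v 10.5% | 7.0 → 5.25 | 2.0 → 2.0 | 2.16 → 2.12 |

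In the 4% v 8% case the number needed to treat moves from 1/0.04 = 25 to 1/0.03 = 33.

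**Step 4. Effect on a derived relapse figure.** If late-pregnancy quitters are spread evenly over recruitment and their true relapse is r, recorded relapse = 1 − 0.75 × (1 − r). An assumed 30% becomes 47.5%, 50% becomes 62.5%, and 70% becomes 77.5%.

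**Step 5. Power.** Normal approximation, two-sided 5%, comparing 352 per arm at the undiluted rates with 470 per arm at the diluted rates:

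- 4% v 8%: 60.9% restricted, 60.2% diluted.
- 7% v 14%: 85.9% restricted, 84.9% diluted.

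Restricting the denominator therefore loses no power. The 235 women carry no 6-month information under either approach.

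**The case against.** The strongest reply is that the document never says women not yet due count as missing. Missing data can fairly be taken to mean data that were due and not obtained. The 75% limit is disclosed as a planned feature, separately from loss to follow-up. On that reading the 6-month denominator was always going to be the women who could reach the time point, and its exact definition belongs in the full protocol or the analysis plan, neither of which is shown. This stands in part. A reader might infer that the trial will certainly code 235 women as smokers; the text allows that but does not say it.

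What does not fall away is that the rule is stated without qualification, beside an intention-to-treat default and a sentence promising contact with every woman. The narrower reading is possible, but nothing in these sections selects it.

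Three further limits stand in full:

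- **Treatment comparison.** A reader might infer that the 6-month comparison is invalid. It is not: with 1:1 permuted-block allocation late recruits should be close to balanced, and the planned logistic model estimates an odds ratio, which hardly moves.
- **Economics.** A reader might infer that the 6-month cost per quitter will be wrong. The Objectives name that quantity, but the economic methods are left to a separate paper and nothing shown says how 6-month quitters enter it.
- **Relapse.** Relapse among late-pregnancy quitters is not a listed outcome. Step 4 describes what would happen to such an estimate if it were derived from these data.

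**Conclusion.** The point holds as a conflict in the text with a definite consequence if the missing-data rule is followed as written: absolute 6-month abstinence rates and the risk difference are scaled by 0.75 in both arms, and any relapse figure built on them is overstated. The primary outcome is unaffected, the risk ratio is unchanged, and the odds ratio and power are nearly so.

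This rests on the following:

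- about 25% of 940 women really are not followed to 6 months;
- those women are treated as missing and not as outside the analysis set;
- they are split evenly between arms.

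The factor 0.75 is relative to the rate among women due for follow-up. It equals the dilution of the rate for all 940 only if late recruits would have quit at the same rate. The percentages in the examples are assumed.

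It should be fixed, but it does not threaten the trial's main conclusion. The documents do not support calling it an established analysis error.

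**What to change.** 1. Define the 6-month analysis set as all randomised women, in either arm, whose expected delivery date plus 6 months falls on or before a follow-up closing date fixed in advance. Membership then depends only on dates known independently of allocation.
2. In Missing data, limit the smoking assumption at 6 months to women in that set who were due and not reached.
3. Use the same set for point abstinence, continuous abstinence and any 6-month cost per quitter or relapse estimate.
4. Reconcile Sample size and recruitment, Participant timeline and data collection, and Follow-up 5 on who is followed to 6 months.
5. State the resulting denominator. It will be roughly 75% of 940, but 705 need not follow exactly. The document describes the followed group by order of recruitment, gestation at enrolment varies, and no closing date is given.

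The cost is wording in the protocol and analysis plan and a smaller stated denominator for the 6-month outcomes. Under the assumptions above there is essentially no loss of power.
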